## Methods and design

### Design

This is a parallel, two-arm, randomised, open-label, multicentre (13 sites in France), prospective study comparing the superiority and safety of an algorithm-guided rituximab regimen with the standard regimen in adult patients with membranous nephropathy. The study will last 7 years, with a 6-year enrolment period and 1 year of follow-up. An overview of the study is shown in figure 1.

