### Sample size

Sample size calculation was performed according to the sequential design method in order to consider the implementation of three interim efficacy analyses. The sample size was calculated with SAS applying the SEQDESIGN procedure, considering the risk of increasing the alpha risk due to multiple analyses. The method used in our case was the O’Brien-Fleming type of boundary (design method=obf) to maximise our chance of stopping the study at the final analysis, if we cannot reach a positive conclusion during the interim analyses.

The criteria applied for the sample size calculation were a total alpha risk at 0.025, with an estimated result of 75% remission in the personalised arm (number of rituximab doses defined by the algorithm) versus 50% in the standard arm (rituximab 1 g×2) and a one-sided sample test for the difference between two binomial proportions. These assumptions about remission rates are based on observations from a retrospective cohort comparing remission rates in patients with rituximab underdosing with those in patients without rituximab underdosing.^10^

Finally, to maintain the total alpha risk at 0.025 and the total beta risk at 0.2 with four analyses, we need to enrol 130 patients in our study, which accounts for a 5% rate of lost to follow-up (anticipated as minor in this study as patients are intensively followed for this pathology).

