### Statistical methods

Our analysis strategy will consider two populations.

ITT population: all patients included in the control or experimental group, whether or not they completed the treatment schedule and had all the biological samples required by the protocol. For the ITT analysis, and in the case of a significant number of lost to follow-up patients (estimated to be 5% for the protocol) that would challenge the robustness of the result, the ‘last observation carried forward’ strategy will be used to impute the missing data for the primary objective.Per-protocol (PP) population*:* all patients enrolled in the study who completed the treatment schedule and had all the biological samples required by the protocol.

As indicated in the sample size calculation, three interim efficacy analyses will be performed. The aim of these interim analyses is to demonstrate the positive effect of increasing the rituximab dose according to the patient’s risk level on the remission rate in order to apply this algorithm as soon as possible.

To maintain the alpha risk at 0.025 with a beta risk equal to 0.2 for the final analysis and to limit the possibility of a chance of a positive interim finding, each interim analysis was planned with:

A one-sided significance level of 0.0002248 was allotted to the first efficacy interim analysis (n=44).A one-sided significance level of 0.00209 was allotted to the second efficacy interim analysis (n=66).A one-sided significance level of 0.00969 was allotted to the third efficacy interim analysis (n=98).A one-sided significance level of 0.02144 was retained for the final analysis (n=130).

The rate of clinical remission observed at 6 months from the first rituximab injection (primary outcome) in the two groups will be compared with access to the significance level, applying a one-sided test for the difference between two binomial proportions (χ^2^ test or Fisher’s exact test in case of a small sample). As the experimental and control groups differ only in the dose of rituximab, with a higher or equivalent dose in the experimental group, a two-sided test is unnecessary in our study.

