In case of a statistically significant result at an interim analysis (p value under significance level), the independent committee will decide the termination of the trial (the interim analysis becomes the main analysis). Any retreatment with immunosuppressive therapy (including rituximab) not planned in the protocol before the end of the study at month 12 will be considered a treatment failure (ie, absence of remission). The statistical tests used, parametric or non-parametric, will consider the total number of patients and the distribution of the variables collected.

For secondary objectives, rates of complete and partial clinical remission at month 12 will be compared using a one-tailed test for the difference between two binomial proportions. Changes in biological samples at 3, 6, 9 and 12 months will be evaluated first by analysis of variance if the normal distribution hypothesis is met and second by a paired Student’s t-test or non-parametric Wilcoxon’s S-rank test, as recommended. For longitudinal analyses, secondary outcomes will be analysed using a linear mixed model to account for repeated measures, including fixed effects for time and intercept random effects for patients. The variables of interest and adjustment will be primarily age and sex, given the total number of patients and the distribution of the variables collected.

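### Read literally, the rule for early stopping leaves about 11 randomised patients not yet at month 6 out of the main analysis, against the plan's own ITT population

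*Protocol article*

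**What the plan says.** All places are in the protocol article.

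- **Statistical methods, stopping rule.** If an interim p value is below its level, "the independent committee will decide the termination of the trial (the interim analysis becomes the main analysis").
- **Statistical methods, ITT population.** It comprises "all patients included in the control or experimental group, whether or not they completed the treatment schedule" and whether or not all required samples were obtained.
- **Statistical methods, looks.** Three interim efficacy analyses at n=44, 66 and 98 and a final one at n=130, with one-sided levels 0.0002248, 0.00209, 0.00969 and 0.02144. Each compares remission at 6 months.
- **Design.** "The study will last 7 years, with a 6-year enrolment period and 1 year of follow-up". No pause in accrual before a look is mentioned.
- **Follow-up.** Visits are scheduled to month 12.

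The article does not say what happens, after a crossing, to patients randomised but not yet at month 6. It specifies a test and names no effect estimate or interval.

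**The concern.** The stopping rule does more than settle the hypothesis test. It fixes which analysis is the main one: the interim analysis. If enrolment continues while a look is being reached, some patients have been randomised and treated but are not yet due for their month-6 assessment. They belong to the ITT population as defined but not to the n=44, 66 or 98 on which the interim test is run. For the main analysis, the two statements then cannot both be followed to the letter.

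At stake is the completeness of the main result after an early stop, which under the planned effect is how most positive trials would end. The missing outcomes would all be due within 6 months, from patients scheduled for visits to month 12 in any case. The provision to carry forward the last observation does not settle the matter, because it is written for patients lost to follow-up, not for those whose visit is not yet due.

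**Working it through.** **1. The plan's own design reproduces.** Inputs from Sample size: "a total alpha risk at 0.025, with an estimated result of 75% remission in the personalised arm", "versus 50% in the standard arm (rituximab 1 g×2) and a one-sided sample test for the difference between two binomial proportions", beta 0.2 and four analyses. The stated levels correspond to z = 3.509, 2.864, 2.338 and 2.025. For an O'Brien-Fleming boundary z_k = C/√t_k, so t_k = (2.025/z_k)² = 0.333, 0.500, 0.750 and 1. Integration of the multivariate normal with these boundaries gives a total one-sided alpha of 0.0250, or 0.0249 at the actual fractions 44/130, 66/130 and 98/130.

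The drift for 80% power is 2.835. With pooled variance (mean rate 0.625):

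n per arm = 2.835² × 2 × 0.625 × 0.375 / 0.25² = 60.3, so 61 per arm and 122 in total.

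122/0.95 = 128.4, so 129 with 5% losses, against 130 stated.

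**2. Patients pending at each look.** Assumptions: uniform accrual over the stated 6 years, no pause, and each look taken when the stated n have reached month 6.

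Rate = 130/72 = 1.81 per month. Pending = 6 × 1.81 = 10.8.

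| Look | n at month 6 | Randomised by then | Pending share | Calendar month |
|---|---|---|---|---|
| 1 | 44 | 54.8 | 10.8/54.8 = 20% | 44/1.81 + 6 = 30 |
| 2 | 66 | 76.8 | 10.8/76.8 = 14% | 43 |
| 3 | 98 | 108.8 | 10.8/108.8 = 10% | 60 |

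All three looks fall before month 72, so enrolment would still be open. If the 130 patients were enrolled in 4, 3 or 2 years, the number pending would be about 16, 22 or 33.

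**3. What including them changes.** Simulation of 500,000 trials: 75% vs 50%, 22/33/49/65 per arm, pooled z-test, stated levels, no losses, and 5 pending patients per arm added after a crossing. Values are differences in percentage points; the true difference is 25.

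| Stop at | Probability | Mean, interim data only | Mean, with pending | Still past the same boundary |
|---|---|---|---|---|
| Look 1 | 0.026 | 56.7 | 50.8 | 78% |
| Look 2 | 0.190 | 39.6 | 37.7 | 87% |
| Look 3 | 0.381 | 28.7 | 28.3 | 94% |
| Any interim | 0.598 | 33.4 | 32.3 | |

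The fourth column can be checked by hand, because pending patients contribute the true difference on average: (22 × 56.7 + 5 × 25)/27 = 50.8; (33 × 39.6 + 5 × 25)/38 = 37.7; (49 × 28.7 + 5 × 25)/54 = 28.3. Simulated power is 0.838, so 0.598/0.838 = 71% of positive trials would stop at an interim.

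**4. Would an adjusted estimate remove the rest?** A stage-wise median-unbiased estimate, solved at about the mean observed differences (normal approximation), leaves 56.7 at 56.7, moves 39.7 to 39.3, and moves 28.7 to just under 28. The change is 0 to 1 point.

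**The case against.** The sentence can be read as ordinary group-sequential language: the analysis that crosses is the confirmatory test. Nothing in the article says that pending patients are excluded, left unfollowed or unreported. The ITT definition covers all patients, and the Follow-up section keeps patients under evaluation. Handling of patients who overrun a look, and estimation after a stop, may also be set out in a full protocol or SAP that is not shown.

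Most of this stands. The exclusion is an inference from the rule together with continued accrual. Three stronger readings are tempting, and the documents do not support them:

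- **That the plan declares the pending patients dropped.** It does not. The conflict with ITT arises when the stopping sentence is taken at its word.
- **That the rule installs an inflated headline estimate.** The article names no estimate. Overestimation after an early stop occurs in any group-sequential trial. Here it is about 4 points at look 3, which accounts for 0.381/0.598 = 64% of interim stops, and the 57-point figure belongs to a 2.6% event. Over all trials, stopped or not, the mean is 27.3 against 25.
- **That the false-positive rate is at risk.** The stated levels hold one-sided 0.025.

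The objection does not remove the sentence itself. It says which analysis is the main one, and a later document that made the full randomised cohort primary would contradict it.

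**Conclusion.** The concern holds as a fault of wording with a practical consequence. As written, an early stop makes the n=44, 66 or 98 analysis the main one. On uniform accrual over 72 months without a pause, that leaves about 11 randomised patients (20%, 14% or 10%) outside the main result, in conflict with the ITT population of the same section. Faster accrual would raise the number; a pause before each look would lower it.

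Type I error is intact. Leaving these patients out explains little of the overestimation after an early stop: including them lowers the mean over interim stops by only 1.1 points, from 33.4 to 32.3, though by about 6 points at look 1. The case for including them rests on ITT and precision. The simulated figures assume 75% vs 50%, no losses and 10 pending patients per look.

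**What to change.** Replace the parenthesis in the stopping rule with three statements:

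- A boundary crossing decides rejection of the null hypothesis and stopping of the trial, and nothing else. The rejection stands whatever the later data show. This needs saying in advance because, under the planned effect, 22%, 13% and 6% of crossings at looks 1, 2 and 3 would fall back below the same boundary once pending patients are added.
- All patients randomised by then are followed to month 6.
- The main ITT effect estimate uses all of them and is shown beside the interim result.

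The report should also acknowledge that an estimate after an early stop tends to be too large: by about 4 points at look 3 under the planned effect, and by more at looks 1 and 2. A stage-wise median-unbiased estimate may be given, but should not be presented as the cure, since it changes the figure by only 0 to 1 point.

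Cost: a change of wording and a wait of up to 6 months for the main report, with no new data collection because visits already run to month 12. The stopping decision itself is not delayed. The reported effect becomes slightly less favourable on average.

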**Methods:**

A multicentre, randomised, controlled, open-label, prospective superiority clinical trial will be conducted in 13 French hospitals. 130 consecutive patients with primary membranous nephropathy and active nephrotic syndrome will be randomised to either the standard protocol control group (two 1 g rituximab infusions on days 0 and 15) or the algorithm-driven rituximab treatment group. In the latter, the rituximab dose will depend on the algorithm-estimated risk of underdosing. Patients with an algorithm-estimated risk of underdosing ≤50% will receive 1 g of rituximab on days 0 and 15. Patients with an algorithm-estimated risk of underdosing between 51% and 75% will receive 1 g of rituximab on days 0, 15 and 30. Finally, patients with an estimated risk of underdosing >75% will receive 1 g of rituximab on days 0, 15, 30 and 45. The primary study outcome is the rate of clinical remission (complete or partial) at month 6 after treatment initiation. The secondary outcomes include clinical remission at month 12, immunological remission, proteinuria, albuminuria, serum creatinine, estimated glomerular filtration rate, phospholipase A2 receptor type 1 antibody titre, anti-rituximab antibody occurrence, lymphocyte count, serum rituximab level and related adverse events.

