### Inclusion criteria

Patients will be recruited if they fulfil the following criteria: age ≥18 years; membranous nephropathy diagnosed by either the presence of circulating anti-PLA2R1 or anti-thrombospondin type-1 domain-containing 7A (THSD7A) antibodies or kidney biopsy; active nephrotic syndrome defined by proteinuria >3.5 g/24 hours (or urine protein-creatinine ratio >3.5 g/g) and serum albumin <30 g/L at screening; estimated glomerular filtration rate (CKD-EPI formula) >30 mL/min/1.73 m^2^; indication for rituximab treatment according to the 2021 KDIGO and French guidelines; non-immunosuppressive antiproteinuric treatment at a stable dose for 2 weeks, including a renin-angiotensin-aldosterone system inhibitor, a diuretic and a low-salt diet at the maximum tolerated dose (ie, absence of orthostatic hypotension and no increase in serum creatinine >30%); social insurance; and signed informed consent (online supplemental file 1). Women of childbearing age must use an effective method of contraception up to 12 months after the last rituximab dose is received.

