### Evaluation criteria

The primary endpoint is the clinical remission 6 months after the first rituximab infusion. Clinical remission is defined as a composite criterion, combining according to KDIGO guidelines: (1) complete clinical remission, defined as urinary protein/creatinine ratio (UPCR) <0.3 g/g in a morning spot urine sample and serum albumin >30 g/L and (2) partial clinical remission, defined as UPCR <3.5 g/g with a decrease >50% from baseline (ie, first rituximab infusion) and improvement or normalisation of serum albumin.

Secondary endpoints include complete clinical remission at month 12; partial clinical remission at month 12; immunological remission (ie, negative antibody titre by ELISA or negative indirect immunofluorescence) at month 3, month 6, month 9 and month 12; changes in proteinuria and albuminuria from baseline to month 3, month 6, month 9 and month 12; changes in serum creatinine and CKD-EPI estimated glomerular filtration rate from baseline to month 3, month 6, month 9 and month 12; changes in anti-PLA2R1 antibody ELISA titre from baseline to month 3, month 6, month 9 and month 12 (patients with PLA2R1-associated membranous nephropathy only); occurrence of anti-rituximab antibodies at month 3, month 6, month 9 and month 12; residual serum rituximab level at month 3 after the first rituximab infusion; recording adverse events related to treatment during study follow-up; changes in lymphocyte counts: B cells (CD19, transitional, mature and memory) and T cells (CD3, CD4, CD8 and T-Reg); changes in non-immunosuppressive antiproteinuric treatment during study follow-up; assessment of clinician satisfaction with the algorithm used to calculate the risk of rituximab underdosing (in the experimental group only); predictive rate (%) of the algorithm for rituximab underdosing in the control group; pharmacokinetics in all patients with serum creatinine and serum albumin levels, weight, anti-PLA2R1 and rituximab level at day 0, day 15, day 30, day 45, month 3 and month 6; and plasma cytokine levels after non-specific stimulation of innate and adaptive immunity cells in pg/mL (interferon (IFN)-γ, IFN-α, interleukin (IL)-12p70, IL-17A, IL-4, IL-5, IL-10, IL-1 and IL-6) at day 0 and month 6.

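### Month-12 remission is named as one outcome in the abstract but split into complete and partial in the endpoint list, and partial remission gets its own one-tailed test without a statement of whether it excludes complete remission

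*Protocol article*

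**What the plan says.** Three places in the protocol article bear on remission at month 12.

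- **Abstract, Methods.** The primary outcome is clinical remission, complete or partial, at month 6. The text continues: "The secondary outcomes include clinical remission at month 12". No split is made there.
- **Evaluation criteria.** The secondary list has two items: "complete clinical remission at month 12; partial clinical remission at month 12". The combined outcome is not listed for month 12. Under the primary endpoint, the first component is "complete clinical remission, defined as urinary protein/creatinine ratio (UPCR) <0.3 g/g in a morning spot urine sample and serum albumin >30 g/L"; the second is "partial clinical remission, defined as UPCR <3.5 g/g with a decrease >50% from baseline", the latter also requiring that serum albumin has improved or normalised. The partial definition has no lower UPCR limit and no clause that removes complete remitters.
- **Statistical methods.** The month-12 analysis is set out as follows: "rates of complete and partial clinical remission at month 12 will be compared using a one-tailed test for the difference between two binomial proportions". The reason for one-sided testing is given for the primary outcome: the experimental dose is never lower than the control dose, so "a two-sided test is unnecessary in our study".

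**The concern.** A one-tailed superiority test suits an outcome whose rate rises whenever patients do better. Complete remission is such an outcome, and so is complete-or-partial remission. Partial remission as a separate category is not: each patient who moves from partial to complete remission lowers its rate. The argument that an equal or higher dose can only help does not carry over, because help can itself reduce the rate.

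The wording leaves open whether partial remission is a separate category. Presenting complete and partial as two numbered parts of a composite suggests that it is. The literal definition suggests that it is not. The two readings give different month-12 estimands and can give opposite results. Choosing between them once data are seen would be a post hoc choice. The abstract and the endpoint list also disagree on what the month-12 remission endpoint is.

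**Working it through.** **1. The plan's own figure.** No figure is stated for the month-12 tests. The sample size supplies the total of 130, 1:1 allocation, 5% loss to follow-up and "a total alpha risk at 0.025, with an estimated result of 75% remission in the personalised arm" against 50% in the standard arm. As a check on these inputs, n per arm = (1.960 + 0.842)² × 2 × 0.625 × 0.375 / 0.25² = 58.9. With a four-look O'Brien-Fleming inflation of 1.024, the total is 2 × 58.9 × 1.024 = 120.6, and 120.6 / 0.95 = 127. That is within 3% of 130, so the primary design reproduces and is not in question here.

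**2. Reading A: partial excludes complete.** Let O be overall remission, C complete and P partial. Then P = O − C, and the difference between arms is ΔP = ΔO − ΔC. Partial remission rises only if ΔC < ΔO, is flat if ΔC = ΔO, and falls if ΔC > ΔO.

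*Illustration (assumed rates, 65 per arm):* control 20% complete + 45% partial = 65%; experimental 45% + 35% = 80%. Here z = d / √(2p̄(1−p̄)/65).

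- Partial: d = −0.10, p̄ = 0.40, SE = 0.0859, z = −1.16, one-sided p = 0.88.
- Complete: d = 0.25, p̄ = 0.325, SE = 0.0822, z = 3.04, one-sided p = 0.001.
- Complete or partial: d = 0.15, p̄ = 0.725, SE = 0.0783, z = 1.92, one-sided p = 0.028.

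*Range of splits (assumed).* Overall remission is held at the design values of 50% and 75%, taken to apply at month 12. There are 62 per arm (130 × 0.95 / 2 = 61.75), and the level is one-sided 0.025, assumed because none is stated for secondary tests. Power = Φ[(d − 1.96·SE₀)/SE₁], where SE₀ uses the pooled rate and SE₁ the separate rates.

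| Control C/P | Experimental C/P | ΔP (points) | Chance of a positive partial test | Power, complete | Power, complete or partial |
|---|---|---|---|---|---|
| 10/40% | 15/60% | +20 | 60.7% | 13.1% | 82.8% |
| 10/40% | 25/50% | +10 | 19.9% | 59.6% | 82.8% |
| 10/40% | 35/40% | 0 | 2.5% | 92.5% | 82.8% |
| 15/35% | 45/30% | −5 | 0.5% | 96.3% | 82.8% |
| 10/40% | 45/30% | −10 | 0.1% | 99.6% | 82.8% |

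Every row has the same 25-point overall benefit. The partial test ranges from moderately powered to almost incapable of a positive result; the combined test does not depend on the split.

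**3. Reading B: the definition taken literally.** Patients enter with proteinuria above 3.5 g/24 h ("or urine protein-creatinine ratio >3.5 g/g) and serum albumin <30 g/L at screening"). A fall in UPCR from above 3.5 to below 0.3 g/g is a decrease of more than 1 − 0.3/3.5 = 91%, well beyond 50%, and albumin has gone from below 30 to above 30 g/L. Almost every complete remitter therefore also meets the partial definition. It is almost every rather than every because baseline is the first infusion, not screening, and entry may rest on 24-hour proteinuria. On this reading the partial rate is in effect O, power is about 83% on the assumptions above, and movement from partial to complete cannot reverse it.

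**The case against.** The strongest reply is Reading B. On the literal definition the test points the right way and the month-12 counterpart of the primary endpoint is already tested, leaving only a poor label. That stands as far as it goes: the reversal depends on a reading that the document does not fix. But the document does not fix Reading B either, and the two-part presentation leans the other way.

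It may also be said that the rule on exclusive or nested categories belongs in the analysis plan, which is not shown. That is fair for the derivation rule alone. It does not settle the disagreement between the abstract and the endpoint list, or the stated choice to test partial remission one-tailed. The methods sentence alone might be read as one combined rate, but the separate items in the endpoint list point against that.

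A reader might infer more than the document supports:

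- *That the partial test must point the wrong way when treatment works.* It need not. If the gain is mainly in partial remission, it points the right way (first two rows of the table).
- *That the month-12 results would read as showing no benefit, or be untestable.* In the illustration the planned complete-remission test gives p of about 0.001, and a p-value of 0.88 is simply non-significant. The combined endpoint, at 0.028, would itself just miss 0.025.
- *That combined month-12 remission is absent, or that partial remission is the main durability result.* The abstract names the former, and nothing gives the latter that status. With exclusive categories the combined rate is also the sum of the two reported rates.

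**Conclusion.** The point holds as a question of definition and alignment for a secondary endpoint. The abstract and the Evaluation criteria differ on month-12 remission, and the one-tailed partial test is either not monotone in benefit (if partial excludes complete) or a mislabelled test of overall remission (if it does not).

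Under exclusive categories and a fixed 50% versus 75% overall benefit, the chance of a positive partial test runs from about 61% down to 0.1% over the splits tried, against about 83% for the combined endpoint. These figures rest on assumed complete/partial splits, which the document does not give, on month-12 overall rates equal to the design rates, and on an assumed one-sided 0.025 level. They show what can happen, not what is expected. The month-6 primary analysis, the interim boundaries and the sample size are unaffected.

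**What to change.** Align the Abstract, Evaluation criteria and Statistical methods:

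1. Replace the separate partial-remission endpoint with complete-or-partial clinical remission at month 12, using the same composite as the primary endpoint.
2. Keep complete remission at month 12 as the other tested endpoint.
3. State that partial remission, where shown separately, means partial without complete, and report it descriptively by arm beside the other two rates.

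This changes wording in the endpoint list and analysis text only and needs no new data. The tested outcomes then both rise with benefit, so the one-tailed direction is coherent. The price is that partial remission alone no longer has a formal test. The change should be made before any comparative results are seen.

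### Secondary changes in proteinuria, albuminuria and anti-PLA2R1 titre: the test is chosen by a normality check, and neither a log or ratio scale nor a clear between-arm comparison is fixed; a log-scale mixed model would be better

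*Protocol article*

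**What the plan says.** Under Evaluation criteria, the protocol article lists among the secondary endpoints "changes in proteinuria and albuminuria from baseline to month 3, month 6, month 9 and month 12" and, for patients with PLA2R1-associated disease, "changes in anti-PLA2R1 antibody ELISA titre from baseline to month 3, month 6, month 9 and month 12". It does not say whether change means a difference, a percentage or a log ratio.

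Under Statistical methods, the rule for changes in biological samples is that they "will be evaluated first by analysis of variance if the normal distribution hypothesis is met". A further step then follows, which the article words as "second by a paired Student’s t-test or non-parametric Wilcoxon’s S-rank test, as recommended". For longitudinal analyses a linear mixed model is planned, "including fixed effects for time and intercept random effects for patients". On covariates: "The variables of interest and adjustment will be primarily age and sex". Treatment arm, arm-by-time and the baseline value are not named.

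The primary endpoint in Evaluation criteria judges partial remission by "UPCR <3.5 g/g with a decrease >50% from baseline", together with a serum albumin condition. Complete remission uses fixed thresholds (UPCR below 0.3 g/g and serum albumin above 30 g/L). Immunological remission means a negative antibody test.

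**The concern.** Three features of the stated rule work against a clear result.

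- **The data choose the test.** A normality check decides between parametric and rank methods, so the reported test can differ between markers and between visits.
- **The scale is left at plain change.** The remedy offered for non-normality is a rank test, not a transformation, and the mixed model has no remedy at all. Raw change depends heavily on how high the baseline was. A patient going from 14 to 7 g/g changes by -7 and is not in remission: UPCR is not below 3.5 g/g and the fall is exactly 50%. A patient going from 4 to 0.2 g/g changes by -3.8 and has a UPCR in the complete-remission range. Raw change puts the first patient ahead, and ranking the raw changes keeps that order.
- **The comparison between arms is not defined.** The paired t-test and the signed-rank test are within-patient tests. The mixed model names only time as a fixed effect, and the factor in the analysis of variance is not stated.

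At stake is how informative the secondary results are on the markers that would show how the algorithm-guided regimen works.

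**Working it through.** **The plan's own figure.** The article states no power or standard deviation for these markers. Its only sample-size figure is for the primary endpoint, with 50% against 75% remission, one-sided 0.025, power 0.80, four O'Brien-Fleming looks and 5% loss:

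- Per arm, pooled variance: (1.960 + 0.842)² × 2 × 0.625 × 0.375 / 0.25² = 58.9
- Both arms with group-sequential inflation: 2 × 58.9 × 1.024 = 120.6
- Allowing for loss: 120.6 / 0.95 = 126.9, against 130 stated (2.4% lower)

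The total is reproduced closely, and nothing below alters it. Evaluable patients per arm: 130 × 0.95 / 2 = 61.75, taken as 62.

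**Range of the marker.** Entry above 3.5 g/g and complete remission below 0.3 g/g: 3.5 / 0.3 = 11.7, so more than ten-fold.

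**Power under a proportional effect (assumed).** Baseline UPCR log-normal with median 7 g/g and log-SD 0.5, truncated at 3.5; follow-up about 60% lower; 62 per arm; two-sided 5%; one visit; 3,000 simulated trials per setting. All tests are between-arm comparisons.

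| Arm ratio, log-SD of change | t-test, raw change | Rank-sum, raw change | Raw change adjusted for baseline | Log ratio |
|---|---|---|---|---|
| 0.6, 1.0 | 45% | 48% | 59% | 80% |
| 0.6, 0.8 | 56% | 58% | 82% | 94% |
| 0.5, 1.0 | 70% | 72% | 84% | 97% |
| 0.6, narrower baseline | 50% | 50% | 61% | 80% |

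Adjusting the log analysis for log baseline left its power unchanged. Repeat simulations of these cases gave 49-72% (raw t-test), 55-77% (rank or normality-gated), 55-81% (raw, baseline-adjusted) and 81-97% (log). Taken together: about 45-77% unadjusted and 55-84% adjusted, against 80-97% on the log scale. Rejection under the null was 4-6% for every method.

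**Other assumed spreads.** With median 6 g/g, log-SD 0.4-0.6 before truncation, log-change SD 0.6-1.0, and an effect set for about 80% power on the log scale: raw t-test 44-56%, rank-sum 50-63%, raw adjusted 52-66%, log 78-79%.

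**Wide baseline, as a titre might have (assumed log-SD 1.2, no truncation).** Raw t-test 16-24%, normality-gated 29-49%, log 80-82%. This also used 62 per arm. The Introduction puts PLA2R1 in 70-80% of primary cases, so about 62 × 0.7 = 43 to 62 × 0.8 = 50 per arm would contribute a titre, and absolute power would be lower on either scale.

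**Additive effect (counter-case).** Baseline mean 7 g/g, SD 1.5 or 2, roughly normal changes with the same SD: raw change 75-78%, log 51-67%. The order reverses.

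**The case against.** A reader might infer that the protocol prescribes absolute change. It does not: it says only changes from baseline. Untransformed change is the plain reading, but an analysis plan not shown here may fix the scale, the arm terms and the handling of values below the assay limit. The word including in the mixed-model sentence also need not be exhaustive. This stands, and it is why the point concerns the rule that the article does state, not the detail it leaves out.

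A reader might also infer that the trial defines response as a proportional fall, so that raw change contradicts it. That goes too far. Only partial remission has a proportional part, only for UPCR, and it is joined to an absolute threshold. Complete remission rests on fixed limits, antibody response on negativity, and albuminuria has no response definition. For albuminuria and titre the case rests on zero-bounding and likely skew.

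The power figures are not those of the named paired tests, which do not compare arms, nor of the mixed model, which was not simulated. They describe a two-sample comparison of raw change, one way of filling the gap. Log-normal data with a proportional effect also favour the log scale by construction, and the additive case shows the reverse. With baseline adjustment the gap narrows to 12-13 points in two of the four tabulated settings.

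An objection that does not stand is that extra doses go only to higher-risk patients, so that benefit may sit at high baselines and suit raw change. With the effect confined to the upper half of baseline (ratio 0.36-0.4), raw tests gave 46-57% and log 67-84%.

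**Conclusion.** The point holds in a limited form. The article states a data-driven choice of test, names within-patient tests, and gives a mixed model with no named arm effect and no log or ratio scale. For zero-bounded markers that can move more than ten-fold, a pre-specified log-scale model is the better method.

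The gain is conditional. If effects are roughly proportional and spreads are near those assumed, a raw between-arm comparison of UPCR would have about 45-77% power, or 55-84% with baseline adjustment, where the log scale has about 80-97%. A proportional effect is plausible for a marker that starts above 3.5 and can fall below 0.3 g/g, but the article gives no data to confirm it. The documents therefore do not support a flat statement that the trial loses power.

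No inflation of false positives was found in the simulated tests. Only secondary endpoints are touched. This is a cheap improvement, not a threat to the trial's main conclusion.

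**What to change.** Pre-specify one between-arm analysis for proteinuria (UPCR), albuminuria and anti-PLA2R1 titre: a linear mixed model on natural-log values with arm, visit, arm-by-visit and log baseline as fixed effects and a random patient intercept. Report geometric mean ratios between arms at each visit with confidence intervals. State one rule for values below the assay limit, either treating them as censored or setting them to a fixed fraction of the limit. Remove the normality-driven choice of test for these markers. Serum albumin and eGFR can stay on the raw scale. If an existing analysis plan already does this, align the protocol wording with it.

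The cost is wording only, settled before outcome data are examined; no extra patients or measurements are needed. The downsides are that effects are reported as ratios and not as absolute differences, that titre results depend partly on the below-limit rule because many titres may become negative, and that some power is lost if effects are in truth additive.
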